#### Exploratory outcomes

The app compiles a short report (synopsis) of the patient’s answers for the physician. We will explore how well this summary matches the input. For this purpose, we will construct a parser that transforms the text of the synopsis into statistically accessible information. We will embed this information in a vector space and examine the correlation between the first principle components from this vector space and those from the recorded input data. We will also run cluster analyses on both data sources individually and compare the results. Further aspects for the exploratory outcomes are demographics (e.g. age, sex), medical complaints, as well as information about the usage of the app (e.g. number of questions asked, time needed to complete).

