#### Big Data objectives

At the time of the final evaluation, there is an extensive standardized dataset of approximately 1,000 patients. A partial data set is to be evaluated in the context of a machine learning / data mining procedure. The aim is (a) to assess the usability of the data for further purposes (intelligent patient management and diagnostics) and to demonstrate this in a use case (e.g. predicting hospital admission), and (b) to characterize the usage process and to identify possibilities for improvement of the user interface.

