#### Intervention group

In the intervention group, the participant then receives a tablet with the app installed. The participant completes the digital medical history in the waiting area. At the end of the survey, the app generates a report from the participants’ responses, which is subsequently transferred to the EMR via a scanned QR-code. This report is available to the physician before the consultation. No data remains stored on the device itself.

When they are next in line, the participant goes to the doctor’s office for consultation. After the consultation, both the participant and the physician are asked to fill out a short questionnaire. The participant will be asked questions about their satisfaction with the consultation (EUROPEP) and about communication (PSQ) and socio-demographic questions. These questions will be presented on the study tablets using the survey software Limesurvey. Subsequently, each participating patient receives a compensation of EUR 15.

The physician is asked to document the ICD-10-GM code (WHO Version 2019) of the (preliminary) diagnosis, to answer questions about their experience of uncertainty regarding this diagnosis and questions matching those that the participant is asked about communication. Additionally, we will collect data regarding the physicians’ specializations and experience (i.e. year of approbation and year of the first specialist examination).

After 14 to 21 days, we conduct a short follow-up to ask participants about their further treatment (e.g. by their family doctor, specialist treatment and hospital admissions). Participants may answer these questions via an online questionnaire (accessed using a personalized link which is sent per e-mail or text message) or by telephone (interview conducted by a study nurse).

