### Statistical design

We will use descriptive statistics to analyze patient characteristics (i.e. demographics, medical complaints) of intervention and control group. Furthermore, the groups will be compared according to characteristics of the recruitment centers.

The primary outcome “diagnostic accuracy” defines the agreement of a given diagnosis with the determined correct diagnosis. The primary evaluations of the binary endpoint of an adequate diagnosis are performed by a generalized linear mixed-effects model (hierarchical or multilevel model) with logit link function. The group (intervention versus control) and the respective out-of-hours practice are included as fixed effects, and the time period (cluster) as a random effect. The random effect is assumed to be normally distributed on the logit scale. The expected value is 0. The variance is unknown and estimated from the data. The odds ratio for the intervention effect will be reported together with its 95% confidence interval and a p-value for the null hypothesis that the intervention does not increase the diagnostic accuracy. Subgroup analyses will explore whether practice characteristics such as experience or specialization of the physicians have an influence on the strength of the intervention effect. This will be done by extending the model described above. Specifically, the respective practice characteristic as well as its interaction with the intervention effect will be included in the hierarchical model. With regard to the secondary endpoints, the individual items of the respective questionnaires are first presented within the framework of descriptive statistics (median, max, min, percentiles). Differences between the intervention and control group are analyzed for each item of the questionnaires using non-parametric methods. Except for the primary endpoints all endpoints are considered exploratory. Therefore, p-values will not be adjusted for multiplicity. Further explorative evaluations will be conducted using machine learning and data mining procedures: methods that are known to work well with a medium sample size will be used for classifications. These methods should have the potential to capture the structure of the underlying associations. We assume that some effects of inquired symptoms on the suspicion of disease severity are additive and individually assessable while others are more likely to conform to a relation like “at least k of n criteria have to be met and none of the following contra-indications” and are more specific to single diseases. We use elastic nets for classifications, because they perform well with the first class of symptom effects even when the number of inquired symptoms is larger than the number of patients. We will also use random forests, because they structurally have some similarity to decision tree like associations that can handle the second class of symptoms. We will utilize the results from these methods to artificially expand the data set for (or to pre-train) more flexible algorithms, such as support vector machines and artificial neural networks. These will then be used to search for more complicated associations. Medical history information, demographic information, treatment information (e.g. diagnosis, examination findings), and event-sourcing information (tracking of the app-usage of individual patients, e.g. time needed to complete) will be used as input variables. In addition, cluster, association and regression analyses will be performed. Results will be visualized and interpreted. Test data from the overall evaluation will be used to determine sensitivity, specificity, and accuracy of prediction models.

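### The match between synopsis and patient input is assessed by component correlations and cluster comparison, which do not measure whether individual answers were carried over

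*Protocol article*

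**What the plan says.** The Exploratory outcomes section of the protocol article sets the aim: "We will explore how well this summary matches the input". A parser will turn the synopsis text into analysable information, which is then embedded in a vector space. Two comparisons follow. The first is to "examine the correlation between the first principle components from this vector space and those from the recorded input data". The second reads "We will also run cluster analyses on both data sources individually and compare the results"; these are groupings of the data and have nothing to do with the randomised weeks.

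The section names no item-level measure of agreement. It does not give the number of components, the scaling or the embedding, and it sets no threshold for a good match.

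Three other places bear on the point:
- Big Data objectives gives the size of the data: "there is an extensive standardized dataset of approximately 1,000 patients".
- Statistical design gives the status: "Except for the primary endpoints all endpoints are considered exploratory".
- Intervention group shows how the synopsis is used: "This report is available to the physician before the consultation".

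**The concern.** Whether a summary matches its source is a question about single answers: was each recorded answer carried over, and is each statement in the summary backed by an answer? Leading principal components address something else. They describe the directions in which patients differ most, and in binary symptom data analysed unscaled these are set mainly by frequent answers that vary together. An answer given by 1 or 2 patients in 100 may add almost nothing to them. A synopsis that loses all such answers can therefore have nearly the same leading components as the full input.

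The synopsis is the route by which the intervention reaches the physician. If the trial shows no effect, one natural question is whether the app's information did not help or did not arrive. A fidelity check that can miss complete loss of a class of answers is a poor guide to that question. The Background section gives missed severe conditions as a reason for the trial, so loss of low-prevalence or warning answers would be of particular interest.

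**Working it through.** The article gives no figure for this outcome, so there is nothing to reproduce. The check is a simulation of the stated measure.

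**Inputs.** From the article: about 1,000 patients (Big Data objectives). Assumed: the number of items, their prevalence, their correlation, the scaling, and complete loss of the rare items. Two families of structure were used:
- 40 or 100 common items plus 10 to 50 rare items at 1-5%.
- 48 items routed by six chief complaints plus 12 rare items at 1-2%.

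Rare items were independent, linked to the common complaints, or one tightly correlated block.

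**Measure.** Let X be the full input and S the same matrix without the rare items. Component scores come from a singular value decomposition of the centred data (unscaled), or of the centred data divided by each item's standard deviation (standardised). The statistic is the absolute correlation of score k from X with score k from S, for k = 1 to 3. Item-level recall is the recorded positive answers present in S divided by all recorded positive answers. For the deleted items it is 0% by construction.

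**Why scaling matters.** A yes/no item has variance p(1 - p). In the routed structure, the commonest complaint affects 30% of patients. Its items are positive in 50% of these patients and 3% of the others:
- Prevalence: 0.3 × 0.5 + 0.7 × 0.03 = 0.171. Variance: 0.171 × 0.829 = 0.142.
- Rare item at 1%: 0.01 × 0.99 = 0.0099, about one fourteenth of that.
- After standardisation every item has variance 1, so the 12 rare items hold 12/60 = 20% of the total. If they move together they can form a leading component of their own.

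**Results with every rare item lost**

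| Scaling | Rare items | Mean absolute correlation, component 1 |
|---|---|---|
| Unscaled | any structure, 1-2% | 0.998-1.000 |
| Standardised | independent, 1-5% | 0.994-0.999 |
| Standardised | linked to complaints | 0.93-0.997 (lowest single run 0.74) |
| Unscaled | block of 40-50 items at 5% | 0.13-0.68 |
| Standardised | one correlated block | 0.02-0.35 |

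In the first row, components 2 and 3 were also about 1.00 (lowest mean 0.954).

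A smaller unscaled set-up had 100 items and three latent factors, with five rare items at about 1-6% deleted. Components 1 to 3 correlated at 0.999-1.000 in all five runs, while 12.5-13.4% of patients lost at least one positive answer.

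**Patients affected in the routed structure.** With 12 independent items, the expected share with at least one lost answer is 1 - 0.99^12 = 11.4% at 1% prevalence and 1 - 0.98^12 = 21.5% at 2%. Across all routed scenarios the simulated share was about 4-23%; the low end comes from the correlated block, where losses fall on the same patients.

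**Cluster comparison.** K-means with six groups was run on X and on S and scored by the adjusted Rand index:
- Independent or complaint-linked rare items: 0.95-0.99, against 0.97-1.00 for reruns on identical data. The loss is hardly distinguishable from rerun noise.
- Correlated block: 0.96-0.97 unscaled and 0.87-0.90 standardised.

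**The case against.** The strongest reply is that this is an exploratory description in a condensed article. It contains no wrong figure and no contradiction, and detailed metrics may sit in an analysis plan that is not shown. It is true that a missing metric would be no finding. But the article does state its measures, and the point is that they do not answer the question it sets for them.

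Several other objections stand and limit the point:

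- A reader might infer that the correlation always stays near 1.0 when rare answers are lost. It does not. With standardised data and a correlated block it collapses, and the article fixes neither the scaling nor the embedding.
- Apart from the 1,000 patients, every simulation setting is an assumption. The shares of patients affected describe the set-ups, not this trial.
- A reader might infer that the plan would certify a defective synopsis. The article sets no threshold and draws no fidelity verdict; it only explores.
- The Background speaks of severe conditions and does not call them rare. The link from severe conditions to low-prevalence app items is a reasonable inference, not the article's statement.
- The parser is not described as yielding statements that map one-to-one to recorded answers. The synopsis is meant to be short, so raw recall would count deliberate condensation as error unless a rule separates the two.

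**Conclusion.** The point holds as a minor one. The stated measures do not capture item-level agreement, so they do not answer whether the summary matches the input. With the same 0% retention of rare items, the mean first-component correlation ranged from 0.02 to 1.000 depending on scaling and correlation structure. A high value does not show that answers were carried over, and a low value does not show how much was lost. The cluster comparison usually gives no better warning. These ranges rest on assumed item structures and on complete loss of the rare items. The general conclusion rests only on what leading components summarise.

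A reader might go further and infer that the primary result is compromised. The documents do not support that. The primary endpoint compares the attending physician's diagnosis with the expert committee's and is analysed in a mixed-effects logistic model, and no synopsis-match statistic enters either step. The consequence is confined to interpretation: the planned check could not reliably show whether loss in the synopsis helps explain the primary result.

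**What to change.** In Exploratory outcomes, or in the analysis plan, make item-level agreement from the planned parser the main measure of match:

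- the share of recorded positive answers that appear in the synopsis;
- the share of synopsis statements backed by a recorded answer;
- the share of patients with at least one unintended omission or wrong statement.

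Report each overall and separately for low-prevalence items or a list of warning items fixed in advance. Keep the component correlations and the cluster analyses as description, with scaling, embedding and number of components stated.

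No new data are needed. The cost is building a map from synopsis statements to recorded answers and writing, before the comparison is run, the rule that separates intended condensation from omission.

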#### Big Data objectives

At the time of the final evaluation, there is an extensive standardized dataset of approximately 1,000 patients. A partial data set is to be evaluated in the context of a machine learning / data mining procedure. The aim is (a) to assess the usability of the data for further purposes (intelligent patient management and diagnostics) and to demonstrate this in a use case (e.g. predicting hospital admission), and (b) to characterize the usage process and to identify possibilities for improvement of the user interface.

### Setting

Patients are recruited in two out-of-hours urgent care walk-in practices in Lower Saxony, Germany. Both practices are run by a service company of the Association of Statutory Health Insurance Physicians of Lower Saxony (‘Kassenärztliche Vereinigung Niedersachsen’, KVN) and provide urgent care for patients with acute but not life-threatening complaints when other practices are closed. Both practices are located in hospitals that also have emergency rooms, but are not part of those hospitals.

Opening times of practice 1 are the following:

Mondays, Tuesdays, and Thursdays from 7 p.m. to 10 p.m.,Wednesdays and Fridays from 3 p.m. to 11 p.m., and.Saturdays, Sundays, and public holidays from 8:30 a.m. to 11 p.m.

Opening times of practice 2 are the following:

Mondays, Tuesdays, and Thursdays from 7 p.m. to 9 p.m.,Wednesdays and Fridays from 4 p.m. to 9 p.m., and.Saturdays, Sundays, and public holidays from 8 a.m. to 1 p.m. and 4 p.m. to 9 p.m.

Physicians work on a self-employed basis but are required to take shifts. They have different specialties and mostly provide care to patients they have not previously known. As there is no common patient file of different health care providers (e.g. medical specialists, physiotherapists) in Germany, physicians have no information about previous consultations or treatments of the patient.

Expenses are covered by the health insurances which German residents are legally required to have. The vast majority are covered through statutory health insurances, patients do not need to pay deductibles for medical consultations [26]. The minority of residents (11%) that are insured through a private insurance company receive a receipt and can later apply for reimbursement from the insurance company [26].

### Inclusion and exclusion criteria

Participating in the study is voluntary and certain inclusion and exclusion criterions are applied. Patients who meet the following criteria are eligible to participate in the study: (a) Seeking care in one of the participating out-of-hours practices due to acute discomfort, (b) aged 18 years or older, (c) able to declare written informed consent to participate in study. Patients who meet one of the following criteria cannot participate in the study: (a) younger than 18-year-old (legally minor), (b) patients in an apparent medical emergency, (c) patients who require immediate medical treatment, and (d) patients who are unable to consent. Recruited participants are informed by trained study nurses and need to declare consent to participate in the study.

### Data collection

Data collection takes place in the waiting area of the respective out-of-hours practices and is performed by study nurses.

The study nurse approaches patients, checks eligibility criteria, and provides interested patients with study information in the waiting area of the out-of-hours practices (Fig. 2). All approached patients are registered in screening lists. These lists include information about patients’ gender, birth year (requested from the patients) and, if applicable, the reason for non-participation (exclusion criterion, refusal or other). If a patient decides to take part in the study, written informed consent and the signed privacy policy statement are obtained. By declaring written informed consent, participants release the physician on duty from the medical confidentiality obligation. Therefore, the physicians must agree to the analysis of their documentations concerning the participating patients.

To contact participants for a follow-up survey after 14–21 days, contact information (phone number or email address) is requested. To be able to merge data sources, a pseudonym (identification number (ID)) is assigned to each enrolled participant.

After obtaining consent for participation, the patient is assigned to either intervention or control group according to the result of the cluster randomization.

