### Study design

To evaluate the effect of the developed app, a two-center, open-label, cluster-randomized trial (CRT) time-periods as clusters and groups under intervention or control condition will be conducted. In the intervention group, patients use the developed app in the waiting area before the encounter and the obtained information is available for the medical assistants and physicians before the consultation. In the control group, patients use the app after the consultation. The entered information is thus not available before the encounter. Clusters are defined as time periods of one week. In each week one practice is in the intervention group, the other one in the control group. The randomization of control and intervention group takes place before the start of the study in blocks of two weeks (see Fig. 1). Due to the two-weeks-block randomization, it is possible that a practice is in the control or intervention group for a maximum of two consecutive weeks.

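### Recruiting nurses can know the week's arm when they approach patients, and the primary model has no patient covariate; age and sex, already collected, should be pre-specified

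*Protocol article*

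**What the plan says.** The Study design section of the protocol article describes a "two-center, open-label, cluster-randomized trial (CRT) time-periods as clusters". It fixes allocation in advance: "The randomization of control and intervention group takes place before the start of the study in blocks of two weeks", and "In each week one practice is in the intervention group, the other one in the control group". It adds that a practice can stay in the same arm for at most two weeks in a row.

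The Data collection section gives recruitment to the on-site study nurse: "The study nurse approaches patients, checks eligibility criteria, and provides interested patients with study information in the waiting area". It then says "After obtaining consent for participation, the patient is assigned to either intervention or control group according to the result of the cluster randomization". Screening lists for all approached patients hold "gender, birth year (requested from the patients) and, if applicable, the reason for non-participation".

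The arms differ visibly after consent. "In the intervention group, the participant then receives a tablet with the app installed", whereas control participants go to the consultation first and use the app afterwards.

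The Statistical design section spells out the primary analysis as a logistic mixed model: "The group (intervention versus control) and the respective out-of-hours practice are included as fixed effects", with time period as a random effect. Patient characteristics appear in that section for descriptive comparison only.

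**The concern.** In an individually randomised trial with concealed allocation, chance alone decides which patients end up in which arm. Here only weeks within practices are randomised, and patients are recruited afterwards, in a week whose arm is already set. If the recruiter knows that arm, whom to approach, how the study is presented and how borderline eligibility is judged can all vary with it, consciously or not. Two of the exclusion criteria, apparent emergency and need for immediate treatment, leave room for such judgement.

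The primary outcome depends on case mix, because some complaints and patients are harder to diagnose than others. If the enrolled patients differ between intervention and control weeks of the same practice, part of the estimated odds ratio reflects who was enrolled and not the app. The stated model has no term that could absorb this, and the limitations in the Discussion do not mention recruitment that differs between arms.

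**Working it through.** **1. Can the recruiter know the arm?** No sentence says so; it follows from combining several.
- The trial is open-label, and a practice keeps one arm for the whole week.
- The study nurse runs the data collection, and its order (app before or after the consultation) is what distinguishes the arms. After the first participant of a week, at the latest, the nurse has seen the arm.
- A limit of two consecutive weeks in one arm holds only if each two-week block contains one week of each arm for a practice. With blocks of one intervention (I) and one control (C) week, the longest run is two (IC followed by CI); if II were allowed, runs could be longer. So the second week of a block is the opposite of the first and can be deduced before it starts.
- Assignment after consent applies an arm that is already set. The article describes no concealment from the nurse, no separate recruiter and no rule of consecutive approach.

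**2. Does the model protect against a shift in patient mix?** The practice effect removes stable differences between the two sites. The random effect for time period models variation between weeks. A shift in mix that follows the arm within a practice moves with the group term, so neither removes it.

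**3. The plan's own figures.** With 75% and 85%, two-sided 5% and 90% power:

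n per group = [1.960 × √(2 × 0.80 × 0.20) + 1.282 × √(0.75 × 0.25 + 0.85 × 0.15)]² / 0.10² ≈ 334.2, so 335, as stated.

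Design effect 1 + (36 − 1) × 0.01 = 1.35, and 670 × 1.35 / 0.95 = 952. With 18 per one-week cluster, 1 + 17 × 0.01 = 1.17, and 670 × 1.17 / 0.95 = 825. All stated figures reproduce, so the point does not rest on a wrong number.

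**4. Possible size.** The documents give neither a case-mix shift nor an accuracy gap between patient types, so both are assumed. With no true effect:

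false difference = shift in case mix × accuracy gap.

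The rejection rate is for a two-sided 5% z-test with control accuracy 75% and an effective 335 per arm.

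| Shift (points) | Gap (points) | False difference (points) | Odds ratio | Rejection rate |
|---|---|---|---|---|
| 5 | 10 | 0.5 | 1.03 | 5.3% |
| 10 | 10 | 1.0 | 1.06 | 6.0% |
| 15 | 10 | 1.5 | 1.09 | 7.4% |
| 5 | 20 | 1.0 | 1.06 | 6.0% |
| 10 | 20 | 2.0 | 1.12 | 9.3% |
| 15 | 20 | 3.0 | 1.18 | 15.0% |

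For the last row: standard error = √[(0.75 × 0.25 + 0.78 × 0.22) / 335] = 0.0327, and 0.03 / 0.0327 = 0.92. The chance of exceeding ±1.96 is then 0.148 + 0.002 = 0.150.

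A harsher assumption, a 20-point shift and a 30-point gap, gives 6 points, an odds ratio of 1.42 and a rejection rate of 47%. The planned effect, for comparison, is 10 points, an odds ratio of (0.85/0.15) / (0.75/0.25) = 1.89. The bias could equally run in the other direction and hide a true effect.

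**The case against.** Much can be said for the plan. The sentence on assignment is not false: it ties assignment to the cluster randomisation and claims no concealment. Each practice spends time in both arms, so stable site differences drop out. Both arms use the same app, with the same payment and follow-up. Demographics and complaints will be described by group. The magnitude rests wholly on assumed inputs, and at their low end it is negligible. Adjusting for age and sex leaves selection on complaint or apparent severity untouched. All of this stands and limits the strength of the point.

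Three stronger readings are tempting but not supported.
- A reader might infer that patients choose according to arm, because the arms ask different things of them. Consent comes before assignment, and nothing says that patients are told the week's arm when they decide. The supported route is selection by the recruiter.
- A reader might take the Discussion's remark that elderly people may be less inclined to join a digital study as evidence of imbalance. It concerns representativeness. Reluctance to use an app would apply in both arms, so the remark shows no difference between them.
- A reader might conclude that the effect estimate is biased. The documents show an opening for bias, not that it was used, nor its direction.

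The objection that covariates may be left to an unseen analysis plan does not succeed. The article names the terms of the primary model, and none is a patient characteristic. A by-arm tabulation of the screening lists, by contrast, is a detail that an article may leave out, and its absence alone would not be a finding.

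**Conclusion.** The point holds as a risk that the stated model leaves unaddressed. Allocation is predictable to the recruiter. That is a strong inference from the open-label weekly design and the two-week blocks, although no sentence states it. Selection that differs by arm within a practice is therefore possible, and the primary model cannot correct for it. Under assumed shifts of 5 to 15 points and accuracy gaps of 10 to 20 points, the false difference is about 0.5 to 3 points against a planned 10, and the false-positive rate about 5% to 15%. Nothing in the documents confirms these inputs. This justifies a cheap improvement to the primary analysis; it does not show that the design is invalid or the result wrong.

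**What to change.** - **Primary model.** Pre-specify age and sex as fixed effects in the logistic mixed model, alongside group, practice and the random effect for time period. Both are already collected, and the consultation cannot change them. State that the adjustment removes only the bias these two variables explain.
- **Interpretation.** State that the odds ratio is then conditional on age and sex as well. It is already conditional on practice and the random effect, so the change in meaning is small.
- **Check on recruitment.** Use the existing screening lists to compare approached, refused and enrolled patients by arm: numbers, age, sex and reasons for non-participation. This covers approached patients only and cannot reveal selection in whom the nurse approaches from the whole waiting room, other than through differences in the number and mix approached.
- **What to leave out.** Do not adjust for complaints recorded in the app. Control participants enter them after the consultation, so the consultation may influence them in one arm only.

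The cost is a few sentences of analysis wording and one table. No new data are needed, and neither recruitment nor sample size changes.
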